#### Study Population

The study population will include children aged 3-59 months attending the selected health facilities in both the intervention and comparator districts. The number of children to be screened in each health facility will depend on the proportion of malaria RDT-positive cases over the total number of children meeting the eligibility criteria. Children who do not meet the inclusion criteria, for example, those with a negative RDT result, will be referred within the same health facility for further assessment and appropriate treatment.

#### Sample Collection and Molecular Analysis

Caregivers of children meeting all the inclusion criteria mentioned earlier will be interviewed using a short paper questionnaire to record personal identifiers of the children such as date of birth, sex, date of interview, and residence location. The study staff will approach them as part of their clinical visits.

A blood sample (4 drops) will be collected through finger prick onto a filter paper (Whatman 3MM) to determine the prevalence of *dhfr*, *dhps*, *pfcrt*, and *pfmdr1* mutations. Other molecular markers of antimalarial resistance will be considered for analysis as comparators. Specimens will be labeled anonymously (unique identifying code, study health facility, and date), dried, stored in individual plastic bags with desiccants, and protected from light, humidity, and extreme temperature until analyzed. All samples will be batched and stored at 4 °Cat the Centro de Investigação em Saúde de Manhiça laboratory (until complete sample collection and analysis). *Dhfr*, *dhps, pfcrt, and pfmdr1* genotypes will be determined using nested mutation-specific polymerase chain reaction, sequencing, and/or polymerase chain reaction-restriction fragment length polymorphism. The prevalence of *dhfr* mutations at codons 51, 59, and 108 and *dhps* mutations at codons 431, 437, 540, 581, and 613 and *pfcrt* codons 72-76 and *pfmdr1* codons 86, 184, and 1246 will be calculated among the sampled children, and differences in the proportions of samples with each of these mutations between baseline and endline will be tested using the *z* test.

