### Implementation of Seasonal Malaria Chemoprevention in Africa

Seasonal malaria chemoprevention (SMC) is “the intermittent administration of full treatment courses of an antimalarial medicine during the malaria season to prevent malarial illness, with the objective of maintaining therapeutic antimalarial drug concentrations in the blood throughout the period of greatest malarial risk” [6]. The currently recommended antimalarials for SMC are sulfadoxine-pyrimethamine (SP) and amodiaquine (AQ), which is administered monthly to children aged 3-59 months during the peak malaria transmission season, which typically coincides with the rainy season. A full course of SP and AQ (SPAQ) consists of 1 dose of SP and 3 doses of AQ, which are administered over a 3-day period. SMC typically involves four monthly cycles of SPAQ administration over the course of the malaria transmission season, which is referred to as a full *round*. The intervention can reduce the incidence of clinical episodes and severe malaria by approximately 75% [7]. It has also been shown that the intervention can be delivered safely at scale, achieving high coverage. The Achieving Catalytic Expansion of SMC in the Sahel (ACCESS-SMC) project scaled up SMC in 7 countries between 2015 and 2017, with few adverse drug reactions reported. SMC was associated with a protective effectiveness of 88% over 28 days in case-control studies conducted as part of ACCESS-SMC [8]. In Burkina Faso and The Gambia, the implementation of SMC was associated with reductions in the number of malaria deaths in hospitals during the high-transmission period, of 42% and 57%, respectively [8]. SMC could also avert millions of cases and thousands of deaths among children living in areas with highly seasonal malaria transmission [3]. In terms of cost, a multicountry cost-effectiveness analysis found that the weighted average economic cost of administering four monthly SMC cycles was US $3.63 per child, and ultimately, that SMC is a highly cost-effective intervention that substantially reduces malaria diagnostic and treatment costs [9].

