### Study Design

We will adopt a type 2 hybrid effectiveness-implementation study design that evaluates the effects of a clinical intervention on relevant outcomes while collecting information on implementation [29]. The hybrid effectiveness-implementation study design supports the pursuit of different lines of research simultaneously, which facilitates the more rapid translation and uptake of study findings for policy makers and implementers [29,30]. This study will use mixed methods to address the aforementioned objectives. Assessments of the protective effect of SPAQ, as delivered as part of SMC implementation, will provide evidence on whether this is appropriate in a region where SP resistance is suspected. Evaluating the implementation of SMC will generate knowledge on the feasibility and acceptability of this intervention in situ, including the challenges, barriers, and facilitators in the local context. Such findings can be useful to inform which intervention components are generalizable and which require local adaptation for other settings [31].

Four monthly cycles of SMC drugs will be distributed door-to-door to eligible children aged between 3 and 59 months by community distributors between November 2020 and February 2021 in 2 districts of Nampula Province. SMC tools and protocols used in Sahelian countries where the Malaria Consortium supports SMC delivery will be adapted to the context in Mozambique for this purpose. A third district will serve as a comparison district (the latter will receive standard malaria prevention, control, and case management). Data collection across the study components was conducted between October 2020 and May 2021 (Figure 3).

The methods are organized according to the study objective, described in more detail below, with an overview provided in Table 2 and Figure 3.

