### Study Objectives and Methods: SPAQ Resistance Molecular Marker Monitoring

#### Overview

The purpose of this study is to determine the baseline prevalence of SPAQ resistance markers and any eventual increase after one round (four monthly cycles) of SMC as assessed via molecular markers in the population. Specifically, to detect prevalence over time in the proportion of symptomatic children, using a positive rapid diagnostic test (RDT), residing in 2 districts where SMC will be implemented who carry parasites with *Plasmodium falciparum* dihydrofolate reductase *(dhfr), Plasmodium falciparum* dihydropteroate synthase (*dhps*)*, Plasmodium falciparum* chloroquine resistance transporter gene (*pfcrt*) and/or *Plasmodium falciparum* multidrug resistance gene 1 (*pfmdr1*) mutations, compared with children living in a neighboring district with similar epidemiologic characteristics but not receiving SMC. Children enrolled in both areas will be aged 3-59 months and will have similar clinical and parasitological characteristics. Health facility–based cross-sectional surveys will be conducted in October 2020, before the SMC distribution begins (baseline), and in March 2021, after one complete round of SMC (endline), to measure the prevalence of molecular markers associated with resistance to SPAQ in symptomatic children aged less than 5 years with a positive RDT attending selected health facilities in the intervention and control areas. Monitoring the prevalence of alleles associated with drug resistance will be done by collecting blood samples from symptomatic children with evidence of infection. During the surveys, fingerpick blood samples will be collected on Whatman 903 (10534612) filter papers (dried blood spots). Sample collection will be performed in 2 selected first-level health facilities in each district of the intervention area and also in 4 selected health facilities in the comparator district, with a total of 8 health facilities across all 3 districts. The main outcome measure is the prevalence of molecular markers associated with SP (codons 108, 51, and 59 in *dhfr* and 437, 540, and 581 in *dhps*) and AQ (codons 72-76 in *pfcrt* and 86, 184, and 1246 in *pfmdr1*) resistance in blood samples collected from symptomatic children aged less than 5 years with a positive RDT attending the selected health facilities. The prevalence will be assessed in areas with SMC and with no SMC at baseline and at the end of the project.

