#### Primary Outcome

The primary outcome of this study will be visits to a health facility for suspected malaria by eligible children and confirmation of malaria diagnosis using an RDT during the 5-month study period, which includes a period of 28 days after the final administration of SPAQ.

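### The endline marker survey pools recently treated and untreated cases, so drug selection in the SMC districts can look like a population rise in resistance

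*Protocol article*

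**What the plan says.** All references are to the Protocol article.

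- **Target.** The Overview of SPAQ Resistance Molecular Marker Monitoring wants the baseline prevalence of markers and "any eventual increase after one round (four monthly cycles) of SMC as assessed via molecular markers in the population".
- **Who is sampled.** Prevalence is measured "in symptomatic children aged less than 5 years with a positive RDT attending selected health facilities in the intervention and control areas". Study Populations gives 3-59 months as the SMC age group, and the survey enrols the same ages.
- **When.** Under Study Design, SMC is delivered "by community distributors between November 2020 and February 2021 in 2 districts of Nampula Province". Baseline is October 2020, before any distribution, and endline is "in March 2021, after one complete round of SMC (endline".
- **What is recorded.** Sample Collection and Molecular Analysis describes a short questionnaire recording "personal identifiers of the children such as date of birth, sex, date of interview, and residence location". SPAQ receipt and date of last dose are not mentioned.
- **Analysis.** The same section calculates the prevalence of each dhfr, dhps, pfcrt and pfmdr1 mutation among the sampled children. Differences "between baseline and endline will be tested using the *z* test". No split by SPAQ exposure is stated.
- **Drug cover.** The Introduction cites a definition of SMC whose objective is "maintaining therapeutic antimalarial drug concentrations in the blood throughout the period of greatest malarial risk". The nonrandomized trial follows children for a study period "which includes a period of 28 days after the final administration of SPAQ".

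**The concern.** At baseline no child has had SPAQ for SMC. At endline, cases in the SMC districts mix children who took SPAQ recently with children who did not. In the first group the drug has prevented some infections. If it prevents sensitive infections more often than resistant ones, the infections that still reach a clinic are enriched for resistance markers. The pooled proportion can then rise between surveys while the parasites circulating in the community stay the same.

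The comparator district corrects for a secular trend common to both areas. It cannot correct for this, because the selection arises only where SPAQ was given.

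The Discussion wants marker monitoring as an early warning of lost effectiveness, and the Introduction names enhanced resistance as a risk of SMC. A rise that reflects who was sampled, read as a rise in the population after one round, would misinform that assessment.

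**Working it through.** **The plan's own figure.** The survey is sized for 0% against 5% with 90% power at the 5% level. The pooled two-sided two-proportion formula gives [1.96√(2×0.025×0.975) + 1.2816√(0.05×0.95)]² / 0.05² = 203. The continuity correction raises this to 242, as stated. That figure is not in dispute.

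**Inputs**
- Recent SPAQ receipt c = 0.80. This borrows the coverage assumption of the end-of-round survey; the documents give no figure for receipt within 28 days of a March visit.
- Protection against sensitive parasites, es = 0.75 (reduction in clinical episodes) to 0.88 (effectiveness over 28 days), both from the Introduction. A lower value of 0.50 is an added assumption, used only for the treated share.
- Protection against resistant parasites, er = 0 to 0.40. This is an assumption; the documents give no value.
- True marker prevalence p, held constant from baseline to endline. The Introduction reports dhfr/dhps mutations at 5-6% in one study and possibly above 80% in later work, so p = 5% and 80% are shown.
- 300 analysed samples per area per survey.

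**Share of endline cases that followed SPAQ** (p = 5%, er = 0):

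share = c[p(1−er) + (1−p)(1−es)] / {c[p(1−er) + (1−p)(1−es)] + (1−c)}

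- es = 0.50: 0.420 / 0.620 = 68%
- es = 0.75: 0.230 / 0.430 = 53%
- es = 0.88: 0.131 / 0.331 = 40%

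**Marker prevalence among all endline cases:**

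q = p(1−c·er) / [p(1−c·er) + (1−p)(1−c·es)]

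The last column is the chance that the z test calls the difference a significant rise: Φ{[(q−p)√300 − 1.96√(2m(1−m))] / √(p(1−p)+q(1−q))}, where m = (p+q)/2.

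| p | es | er | q | Chance of a significant rise |
|---|---|---|---|---|
| 5% | 0.75 | 0.40 | 0.034/0.414 = 8.2% | 0.35 |
| 5% | 0.88 | 0.40 | 0.034/0.315 = 10.8% | 0.75 |
| 5% | 0.75 | 0 | 0.050/0.430 = 11.6% | 0.84 |
| 5% | 0.88 | 0 | 0.050/0.331 = 15.1% | 0.99 |
| 80% | 0.75 | 0.40 | 0.544/0.624 = 87.2% | 0.66 |
| 80% | 0.88 | 0 | 0.800/0.859 = 93.1% | 1.00 |

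**Where the shift is nil.** If er = es, the factors cancel and q = p. If p = 0, then q = 0.

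**What separates the explanations.** In this model, cases without recent SPAQ stay at p. With es = 0.75 and er = 0, cases after SPAQ show 0.05 / (0.05 + 0.95×0.25) = 17.4%. Only the pooled figure moves away from the population value without saying why.

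**The case against.** **The list is illustrative and the article is condensed.** This stands. The wording introduces examples of identifiers, and the article says that the full protocol and data collection tools can be requested. A reader might infer that SPAQ receipt is not collected, or that treated and untreated cases cannot be separated. The documents support only that it is not listed. The point survives because the analysis as stated does not use exposure, whether or not it is recorded.

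**The authors do not claim spread.** The Overview goes on to specify a proportion of symptomatic, RDT-positive children. No passage says that a rise will be attributed to spread, or ties this result to a decision to continue SMC. Enrichment among treated cases may itself be useful as early warning. All of this is fair. But the stated purpose still refers to the population, and the pooled comparison cannot tell the two signals apart.

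**The design point is unaffected.** Also correct. The sample size assumes the sextuple mutant at 0%, where selection alone cannot produce a rise. It would be wrong to set the 5% illustration against the 5-point change for which the survey is sized, since that change starts from 0%. The exemption does not cover the other mutations, each of which is tested.

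**The magnitudes lean high.** They assume 80% recent receipt and protection still in force at sampling. The documents give no days for the last cycle or the March survey, so some sampling may fall after 28 days. The Introduction also expects SPAQ to keep some benefit where resistance is common. Allowing 40% protection against resistant parasites brings the 5% case down to about 8-11%, and it would be lower still with less recent receipt.

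**Conclusion.** The concern holds in a limited form. The stated aim refers to the population, while the stated analysis pools recently treated and untreated cases in the SMC districts and sets them against an untreated baseline. For markers present before SMC, this can show a rise with no change in circulating parasites, and the comparator district does not remove it.

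With 80% recent receipt, protection of 75-88% against sensitive and 0-40% against resistant parasites, and nothing changing in the population, a marker at 5% would show as about 8-15%. The planned test would call this a significant rise with probability 0.35 to 0.99. These figures illustrate the mechanism and do not predict its size, because differential protection by genotype is assumed. The shift is nil without that difference, and nil for a marker truly at 0%.

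A reader might infer that most endline cases are breakthrough infections. The same model gives about 40-68% at 5% prevalence: a substantial share, but not reliably a majority. Labelling the whole endline sample as breakthrough cases would therefore be inaccurate.

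**What to change.** 1. At endline, record the number of SPAQ courses and the date of the last dose, from the SMC card or by caregiver report. The nonrandomized trial already relies on cards that hold doses, and the end-of-round survey already asks caregivers about receipt by cycle.
2. Report marker prevalence separately for children with and without SPAQ in the previous 28 days, alongside the pooled figure.
3. Base any statement about a population increase on children without recent SPAQ, compared with baseline and with the comparator district.
4. Describe the pooled endline figure as prevalence among symptomatic cases that include recently treated children.

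The cost is two questionnaire items, one stratified table and lower precision. At the treated shares above (68% to 40%), about 97 to 181 of 300 cases would be without recent SPAQ. At 5% prevalence the 95% half-width, 1.96√(0.05×0.95/n), widens from 2.5 points at n = 300 to between 4.3 points (n = 97) and 3.2 points (n = 181). If sampling is already complete and receipt was not recorded, item 4 and a stated limitation remain possible.

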### Nonrandomized Controlled Trial

#### Overview

A nonrandomized controlled trial will be conducted to determine whether the receipt of SPAQ is associated with a reduction in the odds of clinically significant malaria outcomes and to estimate the protective effect of SPAQ. There will be two arms: one (control arm) in the comparator district and the other in one of the SMC intervention districts. Communities will be randomly selected in both the intervention and control districts. Eligible children (aged 3-59 months at the first SMC cycle) will be recruited through random selection. Exclusion criteria include the presence of a severe, chronic illness and a history of a significant adverse reaction to SP or AQ. Selected children will be treated appropriately and retained during the trial. In the control district, communities bordering the intervention district will be avoided because of potential unintended *leakage* of SPAQ across the district boundary.

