### Study Populations

The study population that is eligible to receive SMC includes afebrile children of either sex, aged 3-59 months, for any of the SMC cycles, residing in Malema and Mecuburi districts. In addition, for the purpose of the end-of-round survey, which includes an indicator measuring the age eligibility of enrolled children, we included children residing in the aforementioned districts, aged 5-10 years, who may inadvertently have received SMC. In addition, health workers who are involved in SMC implementation, caregivers of children aged under 10 years, community leaders, and key stakeholders such as health officials at different levels of the health system and those involved in SMC implementation will be sampled, according to the study objective, described in more detail in the *Methods* section. The Lalaua district will serve as a control area (see Table 1 for estimated population sizes).

**Table 1 table1:** Estimated target population of seasonal malaria chemoprevention implementation districts and comparison district by age (2020).

Target population estimates		Population of children aged 3-11 months, n (%)	Population of children aged 12-59 months, n (%)	Total population, n	

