**Figure 3 figure3:**
[figure not shown]
Timeline of seasonal malaria chemoprevention study objectives. Obj: Objective; RCT: randomized controlled trial; SMC: seasonal malaria chemoprevention; SPAQ: sulfadoxine-pyrimethamine and amodiaquine.

**Table 2 table2:** Overview of research objectives, methods, and sampling.

Objective	Method	Study population	Inclusion criteria	Exclusion criteria	Sample size (N=3320), n (%)
SPAQ^a^ resistance molecular marker monitoring	Quantitative: molecular analysis	Eligible children aged 3-59 months on the day 1 of the first SMC^b^ cycle	Aged 3-59 months attending the health facilities in study area with fever or history of fever in preceding 24 hours, with a positive malaria RDT^c^ and, with prior informed consent obtained from the parents or guardians	Presence of any signs or symptoms of severe malaria, refusal to participate	600 (18.07)
Nonrandomized controlled trial	Quantitative: nonrandomized controlled trial	Eligible children aged 3-59 months on the day 1 of the first SMC cycle	Eligible children, visited home for enrollment	Presence of a severe, chronic illness and a history of a significant adverse reaction to sulfadoxine-pyrimethamine or amodiaquine Refusal to participate	800 (24.09)
Assessment of impact of SMC on reported malaria morbidity indicators	Quantitative: DHIS2^d^ or SISMA^e^ data analysis	Data quality audit and morbidity analysis of all confirmed malaria cases reported in children aged less than 5 years in the 3 study districts from November 2020 to March or May 2021	HMIS^f^ data on health facility attendance for children aged 0-13 years (inclusive) will be extracted from health facility registers as full line listings, covering November 2020 to May 2021	Data from children aged >13 years or those falling outside the specified dates	26 health facilities in all 3 study districts
Process documentation of SMC adaptation	Qualitative: documentation of the adaptation process	N/A^g^	N/A	N/A	N/A
Feasibility and acceptability assessment	Qualitative: KIIs^h^ and FGDs^i^	Health workers implementing SMC Caregivers of children aged 3-59 months, community members, and community leaders Health workers SMC implementers Health officials and policy makers (district, provincial, and national)	Must fall into one of the study population’ categories, must consent to participate	Not categorized into one of the described study populations Refusal to participate	120 (3.61)

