#### Recruitment and Data Collection

Households will be randomly sampled from selected communities in both the control and intervention arms and 1 eligible child recruited at random in each household. A short baseline questionnaire will be administered to collect individual data on each child and to confirm their eligibility after the caregivers provided their consent. In the intervention arm, the questionnaire will be administered before the intake of SPAQ for SMC. The primary end point will be recorded through passive surveillance by study clinicians in both the intervention and comparator areas during the 4-month study period. Children recruited into the study presenting at clinics will be identified using information on SMC record cards, on which a child’s information and SMC doses are recorded, and data on health facility visits including suspected malaria cases and results of RDTs will be matched to baseline questionnaire data to build a database for analysis.

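### Trial entry has no fever or current-malaria rule although SMC eligibility requires an afebrile child, so malaria illness already present at enrolment can count as a primary outcome

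*Protocol article*

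**What the plan says.** The protocol article uses the word *eligible* in two ways.

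- **Receiving SMC**, in the Study Populations section, is defined as follows: "The study population that is eligible to receive SMC includes afebrile children of either sex, aged 3-59 months, for any of the SMC cycles". The sentence is limited to residents of Malema and Mecuburi, the two SMC districts.
- **Entering the trial** (Nonrandomized Controlled Trial, Overview): "Eligible children (aged 3-59 months at the first SMC cycle) will be recruited through random selection". The exclusions follow: "Exclusion criteria include the presence of a severe, chronic illness and a history of a significant adverse reaction to SP or AQ". The trial row of Table 2 gives the inclusion criterion as "Eligible children, visited home for enrollment" and repeats the exclusions, adding refusal: "Presence of a severe, chronic illness and a history of a significant adverse reaction to sulfadoxine-pyrimethamine or amodiaquine Refusal to participate". Neither place mentions fever, acute illness or current malaria.

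At baseline (Recruitment and Data Collection), "A short baseline questionnaire will be administered to collect individual data on each child and to confirm their eligibility". In the intervention arm this comes before SPAQ is taken. No test at enrolment is described.

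The Primary Outcome section counts "visits to a health facility for suspected malaria by eligible children and confirmation of malaria diagnosis using an RDT during the 5-month study period". The Data Analysis section takes a diagnosis at any time in the study period. It adjusts for sex, age, parental education and net use, and the Cox model times failure by the date of attendance.

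**The concern.** A child who already has malaria illness on the enrolment day, attends a facility and tests positive is counted as a primary outcome. SPAQ given that day or later could not have prevented that episode. No stated rule sets it aside, and no listed covariate captures it. In the Cox model it is a failure at or near time zero.

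Two consequences follow.

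1. If these children enter both arms alike, the same fraction of unpreventable events is added to each arm and the estimated protection shrinks.
2. If they enter the arms unequally, the estimate is biased, in a direction that depends on which arm has more of them. This could happen because a site in the SMC district reads *eligible* as including *afebrile* while nothing prompts the same reading in Lalaua, or because entry illness differs between districts. Arms are allocated by district, so randomisation does not balance entry illness.

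**Working it through.** **1. The planned contrast.** The Sample Size section gives a control risk of 0.20, a 40% reduction (hence 0.12), 80% power and a 5% level. The unpooled two-proportion formula gives n = (1.96 + 0.8416)² × (0.20×0.80 + 0.12×0.88) / 0.08² = 325.7, or 326 per arm; the pooled form gives 329. The stated 327 lies between them. 654/0.8 = 817.5, which rounds up to the stated 818. Power at 327 per arm is 79.8%. The contrast 0.20 against 0.12 is therefore the right base.

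**2. Share affected.** The article does not state it. One rough guide is incidence times duration. With 0.2 facility-presenting episodes per child over four months (about 120 days), the daily rate is 0.2/120 = 0.00167. Illness lasting 3-5 days is my assumption:

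- 3 days: f = 0.00167 × 3 = 0.50%
- 5 days: f = 0.00167 × 5 = 0.83%

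On the same basis, 2% would need episodes of 0.02/0.00167 = 12 days, and 5% would need 30 days.

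**3. Effect on the estimate.** Let f be the share of an arm whose illness at entry becomes a counted visit. The observed risk is f + (1 − f) × p, with p = 0.20 (control) or 0.12 (SMC).

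| f | Control with entry cases | SMC with entry cases | Reduction, both arms | Reduction, control only | Reduction, SMC only |
|---|---|---|---|---|---|
| 0.50% | 0.2040 | 0.1244 | 39.0% | 41.2% | 37.8% |
| 0.83% | 0.2067 | 0.1273 | 38.4% | 41.9% | 36.3% |
| 2% | 0.2160 | 0.1376 | 36.3% | 44.4% | 31.2% |
| 5% | 0.2400 | 0.1640 | 31.7% | 50.0% | 18.0% |

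Example, f = 0.50% in both arms: 1 − 0.1244/0.2040 = 39.0%. Control only: 1 − 0.12/0.2040 = 41.2%. SMC only: 1 − 0.1244/0.20 = 37.8%.

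These are risk reductions. The planned analysis reports odds ratios; the design odds ratio is (0.12/0.88)/(0.20/0.80) = 0.545.

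**4. Power with equal entry in both arms, 327 per arm.** 77.4% at f = 1%, 74.9% at 2% and 67.8% at 5%. At 0.5-0.8% the loss is therefore under 2.4 percentage points.

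**5. Does *eligible* already carry *afebrile*?** The molecular marker row of Table 2 describes its study population in the same terms as the trial row, yet its inclusion criteria require fever or a recent history of fever and a positive RDT. In that table the phrase cannot mean afebrile. If the Study Populations sentence is imported instead, it covers the SMC districts only and says nothing about Lalaua.

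**The case against.** **The afebrile condition may govern dosing only.** It is attached to receiving SMC at any cycle, whereas trial entry is defined separately by age and Table 2 gives one set of criteria for the whole trial. Eligibility is confirmed before SPAQ is taken, so a fever check at dosing would come after recruitment. A child febrile at the first cycle can then be in the trial without that dose. This is the plainest reading, and it stands. It points to dilution in both arms and leaves the counting of entry illness untouched.

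**Enrolling children ill on the day is a pragmatic choice.** In a hybrid effectiveness-implementation study analysed by allocated arm, that is defensible. Even so, the choice should be stated and made alike in both districts.

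**The article is condensed.** The listed exclusions need not be exhaustive, and a fuller protocol is available on request. That lowers the weight of the point. However, the article states the criteria twice, in the text and in Table 2, and neither statement fits its own definition of eligibility.

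**A stronger reading.** A reader might infer that protection is overstated because febrile children are screened out in the SMC arm only. At an assumed 2-5%, the apparent reduction would be 44-50%, and an inert drug would show 1 − 0.20/0.216 = 7% to 1 − 0.20/0.240 = 17% protection. The article does not support this as the expected result:

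- A site would have to override the trial's own age-based definition, in one district only.
- The 2-5% is not in the article and needs 12-30 day episodes on its own incidence figure.
- Every such child would have to reach a facility and test positive, although Study Setting says high SMC ranking went to areas with poor access to care and poor treatment seeking.
- Entry cases are added on top of 0.20, which the article gives for all facility-presenting episodes in the season.

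The last two reservations also apply to the smaller figures, which are therefore on the high side for a given f.

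**Conclusion.** The point holds in a limited form. The article's two uses of *eligible* do not agree, trial entry has no criterion on fever or current malaria, and the outcome counts illness already present at enrolment. On the plainest reading the result is mild dilution: about 39.0-38.4% instead of 40%. Control-only entry would give about 41.2-41.9%, and SMC-only entry about 37.8-36.3%. All rest on assumed 3-5 day illness, full later confirmation, and entry cases added to the protocol's risks. An assumed 2-5% would give 36-32% (both arms), 44-50% (control only) or 31-18% (SMC only). The true share, and its balance between districts, cannot be known from the article. The sample size is not in error. The reason to act is that a two-district comparison without randomisation should not leave entry and event counting open to different readings by arm.

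**What to change.** - Reconcile *eligible* across Study Populations, Table 2 and the trial Overview, so that one trial-entry criterion applies identically in both districts, kept separate from the condition for receiving SMC at a cycle.
- Record fever or history of fever on the existing baseline questionnaire in both arms.
- Define the start of the at-risk period so that illness present at entry is not counted as an outcome. Starting the count on the day after enrolment is not enough alone, because a child ill at entry who attends on day 2 would still count.
- Add a sensitivity analysis that excludes early events or children febrile at baseline. A caregiver's report of fever does not detect infection without symptoms.

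The cost is one more question, a few sampled children replaced or set aside, and slightly fewer events. The stated sample size need not change, since the fix restores the 0.20 against 0.12 contrast. This concerns trial entry and event counting only; no view is taken on how febrile children should be managed.
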